# Analysis of the correlation between periodontal disease and metabolic syndrome among coal mine workers

**DOI:** 10.1097/MD.0000000000021566

**Published:** 2020-08-14

**Keywords:** coal mine workers, clinical trials, periodontal disease, metabolic syndrome

## Abstract

**Trial registration::**

ClinicalTrials.gov, ChiCTR2000034177, Registered on 27 June 2020

## Introduction

1

Periodontal disease refers to diseases that occur in periodontal tissue, including gum disease that only affects gum tissue and periodontitis that affects deep periodontal tissue (peridontal membrane, alveolar bone, cementum).^[1,2]^ Periodontal disease is the second largest oral disease after caries, and it is also an important disease that harms human oral health.^[3]^ About 2-thirds of people in China suffer from periodontal disease and are related to a variety of diseases. The early symptoms of periodontal disease are not easy to attract attention, resulting in chronic infection of periodontal tissue and repeated attacks of inflammation.^[4]^ This not only impairs the function of the oral chewing system, but also seriously affects health. Various factors can trigger or promote the occurrence and development of periodontal disease, and become a risk factor for periodontal disease.^[5]^ Metabolic syndrome (MetS) refers to the pathological state of metabolic disorders in the body's proteins, fats, carbohydrates and other substances. MetS is a systemic metabolic disease.^[6]^ It can cause disorder of the internal environment of the body and uncontrolled inflammation, which can be reflected in various organs of the body and cause various diseases.^[7]^ MetS is associated with many chronic diseases. The core of its pathogenesis is obesity and insulin resistance, and it is accompanied by an imbalance of inflammatory mediators and a low-level inflammatory response, leading to multiple systemic diseases in the body.^[8,9]^ The disease has the following characteristics: ① A variety of metabolic disorders are integrated, including obesity, high blood sugar, hypertension, dyslipidemia, high blood viscosity, high uric acid, high incidence of fatty liver and hyperinsulinemia. These metabolic disorders are the pathological basis of heart and cerebrovascular diseases and diabetes. It can be seen that diabetes is not an isolated disease, but 1 of the components of the MetS. ② There is a common pathological basis, and it is currently believed that their common cause is insulin resistance and hyperinsulinemia caused by obesity, especially central obesity. ③ MetS can cause a variety of diseases, such as hypertension, coronary heart disease, stroke, and even certain cancers, including breast cancer related to sex hormones, endometrial cancer, prostate cancer, pancreatic cancer of the digestive system, liver and gallbladder cancer, Colon cancer, and so on.

Periodontal diseases are also part of systemic inflammatory diseases. Among Chinese middle-aged and elderly patients with MetS, periodontal morbidity is very high. This is due to the involvement of inflammatory mediators in the pathogenesis of MetS and periodontal disease. The latter may also be a risk factor for the former's morbidity and promotion of disease progression. At present, there are not many investigations involving periodontal examination data and periodontal disease prevalence of patients with MetS. However, there are no domestic reports on coal mine workers, especially those working underground. This study will explore the relationship between MetS (including management personnel, uphole workers, and downhole workers) and explore the significance of MetS in the occurrence and development of periodontal disease, and investigate and analyze in different positions and different jobs Differences in morbidity in the environment. We will hope to provide a reference for the prevention and treatment of periodontal diseases.

## Methods/design

2

**Figure 1 F1:**
[figure not shown]
SPIRIT figure for the schedule of enrollment, interventions, and assessments.

### Participants

2.2

The subjects of this study will be included in the outpatient and hospitalized patients from the Kailuan general hospital, and meet the diagnostic criteria for MetS.

#### Diagnostic criteria

2.2.1

We will refer to the relevant diagnostic criteria recommended by the Diabetes Branch of the Chinese Medical Association:

(1)Overweight and/or obese BMI≥25.(2)Hyperglycemia fasting blood glucose (FPG) ≥6.1mmol/L (110 mg/dL) and/or 2hPG ≥7.8mmol/L (140 mg/dL), and/or those who have been diagnosed with diabetes and treated.(3)Hypertensive systolic/diastolic blood pressure ≥140/90mm Hg, and/or those who have been diagnosed with hypertension and treated.(4)Blood lipid disorder fasting blood triglyceride ≥1.7mmol/L (150 mg/dL), and/or fasting blood HDL-C <0.9mmol/L (35 mg/dl) (male), <1.0mmol/L (39 mg/dL) (female).

Those with 3 or all of the above 4 components can be diagnosed with MetS.

#### Inclusion criteria

2.2.2

This study will be conducted in China. Patients will be recruited from Plastic surgery departments of the Kailuan general hospital. We will enroll participants based on the following inclusion criteria:

(1)Meet the diagnostic criteria of Western Medicine MetS.(2)Occupation is coal mine employees (including management personnel, underground workers, underground workers).(3)The age is between 20 to 55 years old.(4)Those who have voluntarily signed the informed consent;

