### Interventions

2.3

We will collect the clinical diagnosis and treatment information of the enrolled patients (such as symptoms, syndromes, signs, electrocardiogram and laboratory examination data, physical examination data, and so on). We will focus on checking the incidence of periodontal disease and recording. Establish a database, check every 10 medical records, and make corrections in time to ensure data accuracy. First of all, we will popularize oral hygiene knowledge for the included patients and guide them to brush their teeth correctly and use dental floss. We will perform periodontal examination on the patients’ teeth by site and record the plaque index, gingival sulcus bleeding index periodontal pocket exploration depth and other indicators. After the inspection, the periodontal pockets were rinsed with 3% hydrogen peroxide solution and 0.9% sterile saline. We will repeat the above inspection items and record in the second and fourth weeks of the experiment. None of the patients in the 2 groups received systemic antimicrobial therapy, and the above clinical operations were performed by the same doctor.

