### Statistical analysis.

2.4

(1)Collect clinical diagnosis and treatment information (such as symptoms, signs, electrocardiogram, tongue and laboratory examination data, physical examination data, and so on), establish a database, verify every 10 medical records entered, and correct in time to ensure Data accuracy.(2)The data is analyzed with the help of SPSS25.0 statistical software. The measurement data is expressed by x ± s or M (IQR), the count data is expressed by the composition ratio or rate, and the chi-square test is used for the comparison between the groups. The model analyzes the relationship between relevant syndromes and clinical indicators.

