
This study will explore the correlation between periodontal disease and MetS of coal mine workers. We aim to clarify the role and mechanism of MetS in the occurrence and development of periodontal diseases, guide the prevention of periodontal diseases, and thus reduce the prevalence of periodontal diseases. In addition, this study will help to control the development of periodontal diseases, improve oral health and general health, and reduce the consumption of medical resources caused by periodontal diseases.

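### Only workers with metabolic syndrome (MetS) can enter, so the MetS–periodontal disease correlation named in the title and aim cannot be estimated

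*Protocol article*

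**What the plan says.** **The question.** The title is "Analysis of the correlation between periodontal disease and metabolic syndrome among coal mine workers". The closing paragraph of the Discussion repeats it ("This study will explore the correlation between periodontal disease and MetS of coal mine workers") and adds the aim to "clarify the role and mechanism of MetS in the occurrence and development of periodontal diseases". The Introduction has a similar aim and a further one: to compare periodontal morbidity across job categories (management, uphole, downhole).

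**Who may enter.** Section 2.2 draws subjects from the hospital's outpatients and inpatients, who must attend there "and meet the diagnostic criteria for MetS". Section 2.2.2 makes this inclusion criterion 1: "Meet the diagnostic criteria of Western Medicine MetS". Section 2.2.1 sets the threshold: "Those with 3 or all of the above 4 components can be diagnosed with MetS". No section describes recruiting a worker without MetS.

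**What is compared.** Section 2.3 says "None of the patients in the 2 groups received systemic antimicrobial therapy". Section 2.4 says "the chi-square test is used for the comparison between the groups". Neither says what the groups are.

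**The concern.** A correlation needs both variables to vary. Here the eligibility rule fixes one of them, MetS, at yes for every participant. The study would measure how common periodontal disease is among miners with MetS and would learn nothing about miners without it.

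At stake is the headline question. If the study is run exactly as described, no result, high or low, bears on whether MetS is associated with periodontal disease. The fault lies in eligibility, not in an unstated analytic detail. A fuller protocol or an analysis plan can choose tests and models, but it cannot analyse people who were barred from entry.

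**Working it through.** The article states no sample size, effect size or power, so there is no planned figure to reproduce. The check is structural. It uses an illustrative n = 200 and periodontal prevalences of 67%, 80% and 90%, all assumed; they bracket the article's own background figures (about two-thirds in the Introduction, 80% to 90% of adults in the Discussion).

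**Step 1: the two-by-two table that the eligibility rule implies.** At 80% prevalence:

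| | Periodontal disease | None | Total |
|---|---|---|---|
| MetS | a = 160 | b = 40 | 200 |
| No MetS | c = 0 | d = 0 | 0 |

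**Step 2: the correlation.** phi = (ad − bc) / √[(a+b)(c+d)(a+c)(b+d)] = (160×0 − 40×0) / √(200×0×160×40) = 0/0. The result is also undefined at 67% (134 and 66) and at 90% (180 and 20). The assumed n plays no part.

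**Step 3: the chi-square test.** The expected count in the cell for no MetS with disease is 0×160/200 = 0. The other cell of that row is also 0, so the statistic cannot be computed.

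**Step 4: what the data do and do not identify.** The sample estimates P(disease given MetS) and nothing about P(disease given no MetS). Suppose the first is 85% (assumed), with odds 0.85/0.15 = 5.67. The odds ratio is 5.67 divided by the odds at the unobserved prevalence q:

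| q without MetS | Odds q/(1−q) | Odds ratio |
|---|---|---|
| 50% | 1.00 | 5.67 |
| 67% | 2.03 | 2.79 |
| 80% | 4.00 | 1.42 |
| 85% | 5.67 | 1.00 |
| 90% | 9.00 | 0.63 |
| 95% | 19.00 | 0.30 |

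Neither direction nor size is determined.

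**Step 5: what a comparator would buy (illustration only).** With two equal groups, two-sided 5% and 80% power, n per group = [1.96√(2p̄(1−p̄)) + 0.8416√(p₁(1−p₁) + p₂(1−p₂))]² / (p₁−p₂)², where p̄ is the mean of p₁ and p₂. For 80% versus 90%: [1.96√0.255 + 0.8416√0.25]² / 0.01 = (0.990 + 0.421)² / 0.01, which gives 199 per group. The same formula gives 180 for 67% versus 80%, and 316 for 67% versus 77%. All these contrasts are assumed. They show only that the question becomes answerable once the second row exists.

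**The case against.** **There may be a comparator already.** Sections 2.3 and 2.4 speak of groups, and the flow chart (Figure 2) is not reproduced in the text at hand. This is the best counter-argument, but it does not rescue the design. If one group were meant to be free of MetS, that would contradict sections 2.2 and 2.2.2, and the eligibility text would still have to change. Nor do two groups match the three job categories in the Introduction. What stands is that the groups must be defined as part of the repair.

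**The study has another aim.** The job-category comparison is stated in the Introduction and can be made among MetS patients. A reader might infer that the study can answer nothing; the article does not support that.

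**MetS can be graded within patients.** This stands too. Participants differ in having three or four components, and the components rest on continuous measures (BMI, glucose, blood pressure, triglycerides, HDL-C). Section 2.3 records plaque, bleeding and pocket-depth indices, so within-MetS gradients are estimable. A reader might infer that only three versus four components can be contrasted, or that every metabolic–periodontal association must be dropped. Both go too far. But a gradient among people who all have MetS does not show whether having MetS matters.

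**Could the cost of the narrowed range be put as a required sample size?** Not from this document. It would need an assumed correlation, assumed component prevalences and their dependence, none of which is given. Four independent components at 30% each, for example, imply MetS in 4×0.3³×0.7 + 0.3⁴ = 8.4% of people, against the 25% in the Discussion. Independence also sits badly with the Introduction, which says that the components share a pathological basis.

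**Published prevalence could serve as the reference.** The two background figures differ from each other, and neither describes miners without MetS. Step 4 shows that choosing between them can reverse the sign. A reader might further infer that the authors will present a high prevalence as an effect of MetS; the article states no such analysis, and the point does not need it.

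**Conclusion.** The point holds and should be settled before the study starts. As written, the eligibility rule makes MetS a constant, and the association in the title and aim is not estimable: information on MetS versus no MetS is zero at any sample size. This conclusion needs no numerical assumption, only that sections 2.2 and 2.2.2 mean what they say. The odds ratios and group sizes above are illustrations on assumed prevalences.

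The finding is limited to the MetS versus no-MetS question. Differences by job category, and associations of periodontal indices with the number or values of metabolic components among MetS patients, remain legitimate targets.

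**What to change.** Choose one of two routes before ethics submission. Section 2.6 says that the plan is still to be submitted and that recruitment has not begun.

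**Route A: keep the question.** Remove MetS as an entry condition in sections 2.2 and 2.2.2. Enrol coal mine workers with and without MetS from the same source. Use section 2.2.1 to classify them rather than to admit them, with the same component measurements and periodontal examination for all. In sections 2.3 and 2.4, define the two groups as MetS and non-MetS.

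Cost: fewer MetS patients for any given total, and all metabolic components must be measured in workers who would not otherwise have had a MetS work-up. If recruitment stays in the hospital, non-MetS participants will be workers attending for other reasons. The source and its limits should be stated.

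**Route B: keep MetS-only enrolment.** Restate the title, aim and conclusions as periodontal status by job category and by metabolic severity (component number and values) among coal mine workers with MetS. Make no claim about MetS versus no MetS, and define the groups in sections 2.3 and 2.4 to match.

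Cost: wording only, but the original question is given up.

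Either route may also need the registry entry brought into line; its content was not available for this review.

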#### Exclusion criteria

2.2.3

Patients will be excluded if they meet the following criteria:

(1)Patients with severe diseases such as malignant hypertension, severe arrhythmia, acute myocardial infarction, cerebrovascular accident, and so on.(2)Patients with acute infection, trauma, surgery, diabetic ketoacidosis, and hyperosmolar coma recently.(3)Patients with severe primary diseases such as brain, liver, kidney and hematopoietic system, mental illness and cognitive dysfunction.(4)Patients with tumor and other organ failure;

#### Conditions for participants to suspend and withdraw from the clinical trial

2.2.4

Researchers participating in clinical trials should carefully record the reasons for the suspension of the trial and the relationship with the clinical trial. It is necessary to clearly record the unwillingness of the subjects to continue the clinical trials, put forward the reasons for withdrawing from the clinical trials, and record the evaluation indicators at the time of discontinuation in detail.

(1)The main symptoms are not clear; the extended description of the current medical history is incomplete; the chief complaint or the description of the current medical history does not match the diagnosis of this disease.(2)Incomplete records of tongue coating and pulse of traditional Chinese medicine affect the syndrome judgment of this disease.(3)The lack of or incomplete general information and physical and chemical index information affects the analysis of relevant data.

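### Section 2.2.4 makes record faults, including tongue and pulse notes and a complaint mismatch with an unnamed disease, conditions for withdrawing workers who are already eligible

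*Protocol article*

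**What the plan says.** Under the heading "Conditions for participants to suspend and withdraw from the clinical trial", section 2.2.4 of the protocol article numbers three conditions:

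1. Main symptoms are unclear, or "the extended description of the current medical history is incomplete", or "the chief complaint or the description of the current medical history does not match the diagnosis of this disease".
2. "Incomplete records of tongue coating and pulse of traditional Chinese medicine affect the syndrome judgment of this disease".
3. "The lack of or incomplete general information and physical and chemical index information affects the analysis of relevant data".

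The same section asks the researchers to "record the evaluation indicators at the time of discontinuation in detail". It does not say whether a withdrawn participant's data are analysed.

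Eligibility rests on something else. The inclusion criterion in section 2.2.2 is "Meet the diagnostic criteria of Western Medicine MetS", and section 2.2.1 defines MetS by BMI, glucose, blood pressure and lipids, or by treated diabetes or hypertension. Three of the four components suffice. Section 2.2 takes outpatients and inpatients of the hospital, while section 2.2.2 says "Patients will be recruited from Plastic surgery departments of the Kailuan general hospital".

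**The concern.** A worker can meet section 2.2.1 in full, have a complete periodontal examination under section 2.3, and still satisfy a withdrawal condition because of how the record was written. Three features stand out.

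- **Complaint mismatch.** The disease that the complaint must match is not named; it could be MetS or periodontal disease. People attending as general outpatients or inpatients, or through plastic surgery, may well present with neither. Read literally, the condition could remove many of the people the study sets out to recruit.
- **Tongue and pulse.** Neither is part of eligibility or of the objective stated in the Introduction and Discussion, which is the relation between periodontal disease and MetS, with differences by job. Pulse is mentioned nowhere else in the article.
- **Incomplete general or laboratory data.** A missing-data problem is answered by withdrawing the person.

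At stake are the precision of the periodontal prevalence and of the job comparisons and, under certain patterns of removal, their validity.

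**Working it through.** The article states no sample size, dropout rate or removal rate, so there is no figure to reproduce. The check has two parts.

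**1. Each condition set against eligibility, outcome and planned use**

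| Condition in 2.2.4 | In MetS criteria (2.2.1)? | In periodontal examination (2.3)? | Other stated use |
|---|---|---|---|
| Unclear symptoms, incomplete history | No | No | Symptoms are collected (2.3, 2.4) |
| Complaint or history mismatch | No | No | None |
| Incomplete tongue and pulse records | No | No | Tongue data and a syndrome model in 2.4; pulse nowhere else |
| Incomplete general or laboratory data | Partly (glucose, lipids, BMI) | No | General analysis |

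The first three rows can therefore remove someone with valid MetS and periodontal data. The fourth touches eligibility only where the gap leaves fewer than three components confirmed.

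**2. What removal would do, under assumed rates**

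Inputs: periodontal disease rate p of about two-thirds (Introduction) or 80% to 90% (Discussion), used only for illustration. All removal rates are assumptions.

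*Total loss.* If each of the three conditions removes a share r:
- Independent faults: 1 − (1 − r)³. For r = 5%, 10%, 20% this gives 1 − 0.95³ = 14%, 1 − 0.9³ = 27%, 1 − 0.8³ = 49%.
- Faults falling wholly on the same people: the loss is r itself, that is 5%, 10%, 20%.

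*Precision.* Confidence intervals widen by 1/√(1 − total loss). A total loss of 10%, 20% or 30% gives 1.05, 1.12 or 1.20.

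*Prevalence.* With removal r1 in diseased and r0 in non-diseased workers, the retained rate is p(1 − r1) / [p(1 − r1) + (1 − p)(1 − r0)].
- r1 = r0 (10%, 20% or 30%): no shift at any p.
- r1 = 30%, r0 = 10%: 66.7% becomes 60.9% (−5.8 points); 80% becomes 75.7% (−4.3); 90% becomes 87.5% (−2.5).
- r1 = 10%, r0 = 30%: 66.7% becomes 72.0% (+5.3); 80% becomes 83.7% (+3.7); 90% becomes 92.1% (+2.1).

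*Job-group odds ratio.* With retention s in each job-by-disease cell, the odds ratio is multiplied by (s11 × s00)/(s10 × s01), where the first index is job and the second is disease.
- Removal depends on job only: (0.7 × 0.9)/(0.7 × 0.9) = 1.00.
- Removal depends on disease only: (0.7 × 0.9)/(0.9 × 0.7) = 1.00.
- One diseased cell removed at 30%, the other three cells at 10%: (0.7 × 0.9)/(0.9 × 0.9) = 0.78.
- One non-diseased cell removed at 30%, the other three at 10%: (0.9 × 0.9)/(0.7 × 0.9) = 1.29.

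Bias in the odds ratio thus needs removal to depend on job and periodontal status together. Bias in prevalence needs dependence on periodontal status.

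**The case against.** A reader might infer that these rules bias the sample even when the reason for removal has nothing to do with periodontal disease or MetS. That is not so: such removal costs precision only, as the calculations show. Nor does the article link record completeness to care setting, severity, job or periodontal status, so a claim that the retained patients are mainly inpatients or sicker has no support.

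A reader might also infer that any incomplete record triggers withdrawal. The text is narrower: the second condition is tied to the syndrome judgment and the third to the analysis. Only the incomplete-history item carries no such qualifier.

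Tongue data are not idle either. Section 2.4 collects them and plans a model of syndromes against clinical indicators. That is a good reason to require them for that model, but not to withdraw the person from the study.

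Finally, section 2.2.4 does not say that withdrawn workers leave the analysis, and it asks for their indicators to be recorded. Analysis sets may be settled in a document not shown, and checking every ten records (sections 2.3 and 2.4) may keep faults rare. All this stands and limits what can be claimed about size. It does not remove the problem that the stated withdrawal conditions turn on matters outside eligibility and outcome.

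**Conclusion.** The point holds in a limited form. Section 2.2.4 fixes documentation faults as withdrawal conditions, and the symptom, complaint, tongue and pulse items belong neither to the MetS criteria nor to the periodontal outcome. Followed as written, the section loses eligible workers with usable data.

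The sure consequence is some loss of precision, provided that withdrawn workers are left out of the analysis, which the article leaves open. Bias is conditional on the dependence described above, and no evidence in the article shows it. The shifts of up to about 6 points and the factors of 0.78 and 1.29 illustrate assumed removal of 10% to 30%; they are not estimates for this study. More extreme retention patterns would give larger factors, but nothing in the article points to them.

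The wording should be changed. Section 2.6 says recruitment has not started, so this can still be done beforehand.

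**What to change.** - Stop using the listed record faults as withdrawal conditions and treat them as missing data.
- State that the main analysis includes every consented worker with verified MetS eligibility and a baseline periodontal examination.
- Apply the completeness requirement for tongue and pulse records only to the syndrome analysis.
- Handle missing covariates by multiple imputation, with a complete-case analysis as sensitivity analysis. Do not impute the components that establish MetS, since that would impute eligibility itself.
- Report the amount of missing data, with reasons, by job group.
- Say whether data recorded at discontinuation are analysed.
- Leave any clinical or safety withdrawal as it is.

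The cost is revised protocol wording and a modest amount of extra analysis work.
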